### Sample size calculation

3.3

In this clinical trial, changes in the K-WOMAC will be analyzed and assessed to examine the effect of acupuncture on pain and functional improvements in patients who underwent TKR.

Due to the lack of information about domestic clinical trials to examine the K-WOMAC as a primary outcome for assessing the effect of acupuncture on the knee joint, we referred to a study in which aromatherapy massage was performed on patients with knee arthritis (married women).^[8]^

The changes in the K-WOMAC after 2 weeks of aromatherapy massage or regular massage in the experimental and control groups were −6.10 ± 4.05 and 0.24 ± 4.16, respectively. The difference in the K-WOMAC between the groups was 6.34. In this study, the difference in the K-WOMAC between the experimental and control groups is assumed to be 3.60. We referred to previous studies for standard deviations. The level of statistical significance is set at 0.05 (α, two-tailed), and power (1−β) is set at 80%.

The minimum sample size needed to test the statistical significance was calculated using ‘G∗Power 3.1.9.2’ and was found to be 22 participants per group. Considering a 10% dropout rate, 25 participants per group or a total of 50 participants will be recruited.

### Intervention

3.4

#### Usual care group

3.4.1

The critical pathway (CP) for TKR (Supplemental Digital Content [Appendix 1]) used at the orthopedics department of our institution will be followed as a standard. However, depending on the patient's condition, adjustments may be made for pharmacotherapy and rehabilitative therapy. Rehabilitative physical therapy and pharmacotherapy will be performed according to the schedule proposed in the CP.

##### Rehabilitative therapy following TKR (physiotherapy)

3.4.1.1

Three days after surgery, the patients will start rehabilitation with continuous passive motion and knee extension, quadriceps femoris strengthening exercises, and gait rehabilitation.

1.Continuous passive motion (CPM) of the knee

Patients place their operated leg on a knee joint exercise machine and perform rehabilitative exercises for 30 min after entering their range of flexion in a digital machine. The range of flexion is determined based on the range of motion over which pain at the surgical site is tolerable.

2.Quadriceps femoris-strengthening exercises

Quadriceps set: Patients use their thigh muscles to extend their knee joints for 5 to 10 min and rest for several seconds. This set will be repeated ∼10 times. At least 10 sets are recommended per day.

Straight leg raises: Patients bend the unoperated leg in the prone position and extend the operated leg. They are required to raise the operated leg 15 cm from the floor and maintain their position for 5 to 10 s. This exercise will be repeated 10 times, and at least 10 sets are recommended per day.

Ankle pumps: The muscles in the lower limbs are contracted to pull the feet toward the head, and the position is maintained for 5 to 10 s. After each exercise, the patients rest for several seconds. This exercise will be repeated 10 times. At least 10 sets are recommended per day.

3.Gait rehabilitation

Patients begin walking carefully using a walker or crutches at 3 days after surgery and gradually put more weight on their legs. The body weight is evenly distributed on the walker or crutches while the patients are standing in a comfortable position. The walker and crutches are moved forward by a short distance, and the operated leg is completely extended to allow the heel of the foot to touch the floor first as the patients walk forward. It is recommended that they walk for short periods of time several times during the day since more than 30 min of continuous walking can aggravate swelling or pain.

##### Pharmacotherapy

3.4.1.2

Pharmacotherapy will be performed in accordance with the TKR CP of the orthopedics department of Catholic Kwandong University International St. Mary's Hospital (Supplemental Digital Content [Appendix 1]).

##### Concomitant drugs and combination therapy/contraindicated medications

3.4.1.3

Patients will be required to confirm with the principal investigator whether they can take specific medications or receive treatments concomitantly with acupuncture before taking or receiving them. The name, dosage, dose, and duration of use of any concomitant drugs that are administered will be recorded on the case report form.

Physiotherapy can be performed concomitantly with acupuncture at the discretion of the participant even during the follow-up period.

#### Acupuncture treatment group

3.4.2

The Acu-treatment group is treated with acupuncture, in addition to the treatment for the usual care therapy group. A disposable sterilized needle made of stainless steel (0.2 mm × 30 mm, Spring Handle Needle, DONGBANG Medical Co, LTD) will be used for treatment. The acupuncture points for treatment are GB 29, GB 28, BL 38, ST 36, CV 3, SP 9, GB 34, ST 28, SP 10, and ST 34. All the acupuncture points were used on the TKR-operated side for 20 min. The reporting of this randomized study was based on the Standards for Reporting Interventions in Controlled Trials of Acupuncture (STRICTA). The Acu-treatment group will receive eight treatments (four sessions between 3 and 8 days after surgery and four sessions between 9 and 14 days after surgery) over 2 weeks. A licensed doctor of Oriental medicine with formal education in the field and over 5 years of clinical experience and acupuncture will perform acupuncture according to the intervention schedule proposed in the protocol.

### Inclusion and exclusion criteria

3.5

#### Inclusion criteria

3.5.1

The inclusion criteria are as follows:

1.adult men and women aged 60 years and older and2.patients with a diagnosis of osteoarthritis and listed for unilateral TKR;3.those with normal cognitive function; and4.patients who are willing and able to give informed consent for participation in the study.

#### Exclusion criteria

3.5.2

The following patients are excluded from participating in the trial:

1.those who had undergone total knee arthroplasty due to gout;2.those who had total knee arthroplasty due to trauma;3.those who had total knee arthroplasty due to autoimmune-related diseases such as rheumatoid arthritis;4.those who were participating in other clinical trials;5.those who had a history of participating in other clinical trials within 1 month;6.those who had difficulty writing a research consent form; and7.those who were judged to be inappropriate for the clinical study by the researchers.

### Recruitment, randomization, blinding, and nonblinding

3.6

Advertisements for patient recruitment will be posted on the Catholic Kwandong University International St. Mary's Hospital bulletin boards, along with posters, banner advertisements and internet cafes. All advertisements will be run after IRB approval.

Individuals who have given written consent for participating in the study will be assigned a screening number in order of the outpatient visit at screening. Unblinded subinvestigators who do not influence the research results and analysis will refer to the randomization list that has been prepared by a commissioned professional statistician and will assign participation numbers. Participants will be allocated to the usual care group and the usual care plus acupuncture group at a ratio of 1:1. A block randomization table is generated by an independent statistician, and patients are assigned to one of two groups according to the randomization table. The screening numbers, randomization numbers, and initials assigned to each participant are used as subject identification codes to identify the participant until the end of the clinical trial.

The usual care used in this study is not a clinical investigation product and does not require allocation concealment, since it is administered to all the groups. Moreover, it is impossible to blind the investigator and the participant in each group due to the nature of the study intervention, which is based on the contact between the patient and the medical staff. Instead, the investigator maintains blinding to prevent bias in evaluating the participant. If the clinical trial is completed, all clinical report forms (CRFs) are collected, the database process is terminated, and unblinding will be performed if required for statistical analysis.

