The patients visited the hospital five times for evaluation. The screening (Visit 1, V1) included only those participants who submitted the informed consent form. For screening, the demographic information, medical history, physical examination, vital signs, questionnaire survey, laboratory test, and selection/exclusion criteria will be evaluated. Randomization and group allocation will be performed at screening. Fifty patients were enrolled and randomly divided into two groups. Patients who have passed the screening test will have a TKR and will be hospitalized in ∼2 weeks with usual care or usual care plus acupuncture therapy.

The patients will receive a total of eight acupuncture treatments over 2 weeks after surgery (four sessions between 3 and 8 days after surgery and four sessions between 9 and 14 days after surgery). They will be followed up at 3, 4, and 12 weeks after the end of the intervention. The primary outcomes will be assessed at V1, V10, and Week 4 of follow-up. The safety evaluations include adverse reaction evaluations, vital sign assessments, and laboratory tests. The adverse reaction evaluation will be performed every day during the hospitalization period and continued during follow-up at 3, 4, and 12 weeks after surgery. The vital sign assessment will also be performed daily during the hospitalization period after surgery and at 4 and 14 weeks of the follow-up. Laboratory tests will be performed during screening, at V5 and V9, and at 4 and 12 weeks of follow-up. An economic evaluation will be performed during the treatment period (2 weeks) and at 4 and 12 weeks after surgery and will investigate medical costs and utility (quality of life) to estimate the quality-adjusted life years (QALYs). The Euro-Qol five dimension scale (EQ-5D), a multiattribute health measurement instrument, will be used to assess the quality of life at baseline (Week 1) and at 2 and 4 weeks. Medical costs will also be investigated at baseline (week 1) and at 2, 4, and 12 weeks for a total of four assessments. These evaluations are performed simultaneously with the clinical trial through in-person interviews during the survey period and through in-person interviews, phone calls, and online communication using questionnaires thereafter according to a predefined arrangement with the patient.

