#### Safety and adverse events monitoring

3.8.3

The safety assessment includes

1.adverse reactions,2.vital signs, and3.clinical laboratory testing.

The subinvestigator will record the details of any adverse reactions and the use of concomitant medications during the clinical trial in the case report form. In case of an adverse reaction, the symptoms and signs of the adverse reaction, duration (start date/end date), severity, result, significance, causal relationship to the drug under clinical investigation, and measures taken for its alleviation will be recorded. The names, dosages, duration of administration, reason for administration, etc, of the concomitant medications will be recorded in detail.

Clinical laboratory tests will be performed at screening, V5, V9, FU2, and FU3. Since this study will evaluate the safety of the usual care and acupuncture combination, it differs from clinical studies that evaluate the safety and pharmacokinetic properties of drugs. Therefore, this study conducts clinical laboratory tests for the following items for the purpose of the standard safety lab test:

1.hematology: hemoglobin, hematocrit, red blood cell count, white blood cell count, and differential count, platelet count;2.serum chemistry: glucose fasting, aspartate aminotransferase (AST), alanine aminotransferase (ALT), blood urea nitrogen (BUN), electrolytes (sodium, potassium, and chloride), serum creatinine (SCr), erythrocyte sedimentation rate (ESR), C-reactive protein (CRP); and3.coagulation: D-dimer, fibrin degradation products (FDP);4.γ-glutamyl transpeptidase (γ-GTP), alkaline phosphatase, creatinine phosphokinase (CPK), uric acid, total bilirubin, total protein, albumin, osteocalcin, carboxy-terminal collagen crosslinks (CTX), urine analysis: pH, protein (albumin), glucose, leukocyte esterase, and blood were performed only at screening.

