#### Early termination or dropout

3.8.4

The early termination or dropout criteria are as follows:

1.Violation of the inclusion/exclusion criteria2.Withdrawal of consent for participation3.Adverse reactions (including serious adverse reactions)

Adverse reactions refer to undesirable and unintended signs, symptoms, or diseases and do not necessarily have a causal relationship with the interventions administered during a clinical trial. However, since the present clinical trial involves patients who underwent TKR, adverse reactions may be deemed symptoms or side effects caused by TKR at the discretion of the operating surgeon and principal investigator. Symptoms that the principal investigator deems as unassociated with the intervention of this clinical trial are not classified as adverse reactions that occur during this clinical trial.

4.Poor compliance (compliance below 70% in the final compliance assessment) or inability to comply5.Violation of the clinical trial protocol6.Other reasons deemed valid by the researchers7.Diagnosis of an infection in the recovery room

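### Section 3.6 waives allocation concealment for a reason that does not bear on it, and has unblinded staff allocate from the block list, which leaves enrolment open to selection bias

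*Protocol article*

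**What the plan says.** Four parts of the protocol article bear on this.

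- **Concealment (Section 3.6).** Usual care, described as not being an investigational product, "does not require allocation concealment, since it is administered to all the groups". The next sentence turns to the impossibility of blinding investigator and participant.
- **Who allocates (Section 3.6).** "Unblinded subinvestigators who do not influence the research results and analysis will refer to the randomization list". The list was "prepared by a commissioned professional statistician and will assign participation numbers". It is a 1:1 block table from an independent statistician, and the block size is not given. No envelope, telephone, web or other central release is described.
- **When (Section 3.2 and Table 1).** "Randomization and group allocation will be performed at screening". Table 1 puts participant screening, randomization and baseline K-WOMAC in the same visit, V1. The Abstract has patients divided into groups after screening and consent, and operated on afterwards.
- **Discretion at entry (Section 3.5.2).** The last exclusion criterion covers "those who were judged to be inappropriate for the clinical study by the researchers".

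**The concern.** Allocation concealment means that nobody deciding on a patient's entry can know or foresee that patient's assignment until entry is final. Masking means that the treatment is not recognisable once it is given. The two are independent. Masking is impossible here, as Section 3.6 says, but concealment is not. It matters more when treatment is open, because staff and patients may prefer one arm and no later masking limits the effect of that preference.

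The reason offered, that usual care goes to everyone, has no bearing on the matter. What needs concealing is whether the next patient will also receive acupuncture.

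If someone who can influence entry knows the next arm, a frailer patient can be judged unsuitable, deferred or discouraged when one arm is next, and accepted when the other is. The arms then differ in prognosis before treatment starts. With 25 patients per arm, a few such decisions could shift the comparison. Adjustment for baseline outcome and covariates (Sections 3.9.1 and 3.9.3.1) can remove part of a measured imbalance but not an unmeasured one.

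**Working it through.** **1. Does the text waive concealment, or only leave out the details?** A condensed article may leave the release mechanism to the full protocol, so silence alone would not be a finding. Section 3.6 is not silent. It says concealment is not required and gives a reason, and the procedure beside it is consistent with that: unblinded staff work from the list, with nothing described in between.

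**2. Do the stated safeguards close the gap?**

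| Safeguard | Where | What it protects | Foreknowledge at entry? |
|---|---|---|---|
| Independent statistician prepares the block table | 3.6 | Generation of the sequence | Not prevented |
| Written consent before numbering | 3.6, Abstract | Order of consent and allocation | Not prevented; eligibility can still be judged with the next arm known |
| Screening numbers in visit order | 3.6 | Order of screening | Not prevented; a discretionary exclusion can still follow |
| Allocating staff said not to influence results and analysis | 3.6 | Outcome and analysis | Enrolment not mentioned |
| Blinded assessor | 3.2, 3.6 | Outcome assessment | Not addressed |

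None of them stops the next assignment from being known while eligibility is still open at V1.

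**3. The plan's own sample size (reproduced, not disputed).** Inputs from Section 3.3: difference 3.60; SDs 4.05 and 4.16; two-sided alpha 0.05; power 80%; dropout 10%.

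- Pooled SD = √((4.05² + 4.16²)/2) = √((16.4025 + 17.3056)/2) = 4.105.
- Standardised difference = 3.60/4.105 = 0.877.
- The two-sample t test (noncentral t) needs 21.4, so 22 per group, as stated.
- 22/0.90 = 24.4, so 25 per group and 50 in total, as stated.

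**4. What a selection shift would do (illustration only).** The document does not say how large a shift might be, so a range is assumed: 10%, 20% and 30% of 3.60. The setting is no true treatment effect, the unadjusted t test, and 22 per group.

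- Standard error of the difference = 4.105 × √(2/22) = 1.238.
- Noncentrality = shift/1.238, with 42 degrees of freedom and critical value 2.018.
- Type I error = P(|T| > 2.018) under that noncentral t.

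| Assumed shift | Points | Noncentrality | Two-sided type I error |
|---|---|---|---|
| 10% | 0.36 | 0.29 | 5.9% |
| 20% | 0.72 | 0.58 | 8.8% |
| 30% | 1.08 | 0.87 | 13.7% |

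**5. Why block size belongs in the fix.** In an open-label trial past allocations are known. With a hidden list but a fixed, known block size (sizes assumed; none is stated), the best guess is right (0.5 + 1)/2 = 75% of the time for blocks of 2. For blocks of 4 it is (0.5 + 2/3 + 2/3 + 1)/4 = 71%, and for blocks of 6, by simulation, 68%. These figures measure the predictability of fixed blocks, not the cost of the sentence in Section 3.6.

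**The case against.** The best defence is that the sentence is about usual care and stands next to the remark on blinding, so it probably meant that usual care need not be masked. On that reading nobody intended to leave the sequence open, and envelopes or a web system may be described in the full protocol. Allocation is also given to a separate role, and the table comes from an independent statistician.

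Part of this stands. The sentence may well be a slip for masking. It is still wrong as written, nothing else in the article supplies concealment, and a site following the text would have no reason to conceal.

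The objection also limits what may be claimed. A reader might infer several stronger things that the document does not support:

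- **That the allocating staff see all future entries, are site staff, or judge eligibility themselves.** The text says only that they consult the list and assign numbers.
- **That the person who allocates also records adverse reactions.** Section 3.8.3 says "The subinvestigator will record the details of any adverse reactions", but does not say it is the same person, and that is a question of ascertainment rather than concealment.
- **That surgical and ward staff know the arm at operation.** Allocation precedes surgery, but disclosure to those staff is not stated.
- **That allocation before surgery causes selection bias.** It cannot affect who is enrolled. It can add exits between allocation and first treatment, for which Section 3.8.4 lists "Diagnosis of an infection in the recovery room", and possibly performance bias. No difference between arms in such exits is shown.
- **That concealment alone would bring guessing down to 50%.** With fixed blocks of known size and open treatment it would not.

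**Conclusion.** The point holds in this form: the article states that concealment is unnecessary, the reason given does not bear on concealment, and the procedure described contains no concealment step. Because eligibility, a discretionary exclusion and randomization share one visit, enrolment under the text as written is open to selection bias. This should be corrected in the protocol, because imbalance in unmeasured prognosis cannot be undone after enrolment.

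Its size is unknown. The error rates of 5.9% to 13.7% rest on assumed shifts of 0.36 to 1.08 points, on the plan's SD and on an unadjusted test. They show sensitivity and do not predict the bias. The sample size is unaffected. The finding is that the text permits foreknowledge; the document does not show that anyone has used it or would.

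**What to change.** Delete the sentence on concealment in Section 3.6 and state that allocation is concealed:

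- The independent statistician or the contract research organization holds the list, with varying block sizes that are not disclosed to recruiting staff.
- Each assignment is released singly, by web, by telephone or in sequentially numbered opaque sealed envelopes.
- Release follows only after consent, eligibility and baseline K-WOMAC are recorded for that patient.
- The staff who obtain or open assignments do not judge eligibility or outcomes.

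Consent before allocation is already stated and baseline K-WOMAC is already scheduled at V1, so the visit schedule need not change. The cost is a simple release procedure and a protocol amendment.

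Separate and optional: keep consent and baseline at V1 but open the assignment after surgery, just before V2. This would reduce exits between randomization and first treatment and limit possible peri-operative performance bias. Its cost is shorter notice for booking acupuncture sessions. It is a design improvement and is not needed to correct the error.

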### Rescue therapy and concomitant medications

3.7

If a participant experiences unbearable pain from screening to discharge, he/she may be allowed to take any rescue medication according to the judgment of the medical staff. The rescue medication was as follows in the hospital or after discharge:

1.pethidine HCl 25 mg,2.oxycodone hydrochloride 5 mg, and3.tramadol hydrochloride.

If the participant takes any rescue medication, the date and dose of administration will be recorded in the study participant's log. If concomitant medication is administered during the trial period, the name of the drug, the daily dose, and the duration of administration should be noted on the CRFs.

### Study outcomes

3.8

#### Primary outcome

3.8.1

The primary outcome in this study was the changes from the baseline in the K-WOMAC. The time frame was as follows: screening, day 11 (visit 10, V10), and day 21 (follow-up 2, FU2). The K-WOMAC^[9]^ was used to evaluate the physical function. The WOMAC is an index that evaluates the pain and functional status of patients with degenerative knee arthritis and is widely used as a measure for evaluating symptoms and treatment effects in patients with degenerative knee joints. It is a self-administered questionnaire consisting of 24 items divided into 3 subscales.^[9]^

